#### Primary outcome measures

##### Physical activity

The daily walking duration (24 h) as proxy for physical activity is monitored with a thigh-worn inertial sensor for three consecutive weekdays (activPAL3™, PAL Technologies Ltd., Glasgow, UK) that was shown to be reliable and sufficient to predict habitual physical activity in older adults [48, 49].

##### Functional performance

Function of lower extremities is measured by the Short Physical Performance Battery (SPPB). The test is conducted according to the original protocol [50] and consists of three functional subtests assessing static balance (side-by-side-, semi-tandem-, tandem-stance), strength of the lower extremities (chair rising) and 2,44-m gait speed. It is suggested as a valid and reliable outcome measure for physical performance in community-dwelling older adults [51]. The sum-score of all subtests (ranging from 0 to 12) is used for the primary outcome analyses.

#### Secondary outcome measures

##### Fear of falling

The 6-item Fear of Falling Questionnaire revised (FFQ-R) is used for assessing fear of falling [52]. Each item is rated on a Likert-type scale from 1 (strongly disagree) to 4 (strongly agree). The total possible score ranges from 6 to 24, with higher scores indicating greater fear of falling. Previous research could demonstrate preliminary evidence that the FFQ-R is a reliable and valid instrument for assessing fear of falling in older hip-fracture patients [52]. The original questionnaire was translated into German (forward and backward). Avoidance of activities due to fear of falling is examined with a single-item question.

##### Fall-related self-efficacy

The Short Falls Efficacy Scale-International (Short FES-I) provides information of level of concern about falls for seven activities of daily living [53, 54]. The FES-I was suggested to be a valid tool for assessing also patients with cognitive impairment (MMSE sum score of validation sample: Mean = 20.9; SD = 2.1) [55].

##### Falls

Falls are recorded by implementing falls calendars and weekly telephone calls by the assessment team. This combination was found to be of acceptable accuracy in patients being in a mild to moderate stage of dementia [56]. Patients (and their caregivers) are asked to keep the diary up-to-date and fill it in each day. A fall is defined as “an unexpected event in which the patient comes to rest on the ground, floor, or lower level” [57].

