## Methods and design

This study is a dual-centre, randomised controlled trial with blinded assessors. Participants (*N* = 240) were randomly assigned to one of two groups (multifactorial intervention or usual care control group) in a 1:1 ratio after initial assessment (−T1) and before discharge from inpatient rehabilitation. Computer-generated random allocation was done by an independent randomisation centre (University of Ulm) and sealed envelopes are used. The randomisation of participants was conducted by the interventionists. The study design is outlined in Fig. 1*.*

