#### Applied materials

##### For participants

All participants are provided with a calendar for entering the scheduled home visits of the exercise instructor, lay instructor and assessor as well as for keeping a falls and exercise diary. Every calendar includes a page with the pictures, names and telephone numbers of the study team. Finally, the participants get a folder with changeable sheets for the recommended self-exercises and additional information sheets about walker handling, coping with situations in which they feel less confident about their balance or fearful to fall, environmental hazards and backward chaining.

For the chair-rising exercise the intervention group gets the already mentioned sturdy foam pads if necessary.

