### Control group

Participants allocated to the control group have usual access to standard care. In addition, they get the calendar for assessment dates as well as the extra sheet as memory aid showing the pictures, names and telephone numbers of the assessors.

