**Table 3 Tab3:**
[figure not shown]
Primary and secondary outcome measures, other measures and defined measurement time points (participant, face-to-face by blinded assessors)

^*^List of specific time points in this row. EQ-5D = EuroQol- 5 Dimension; FES-I Short = Falls Efficacy Scale International – Short; FFQ-R = Fear of Falling Questionnaire – revised; F-SozU = Modified version of Social Support Questionnaire; MADRS = Montgomery–Åsberg Depression Scale; NAI: ZN-G = Nuremberg Age Inventory / subscale “repeating numbers” (both forward and backward); QoL-AD = Quality of Life in Alzheimer’s Disease; SPPB = Short Physical Performance Battery WOMAC = Western Ontario and McMaster Universities Osteoarthritis Index / subscale pain

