**Table 4 Tab4:**
[figure not shown]
Secondary outcome measures, other measures and defined measurement time points (participating caregiver, written and, if necessary, face-to-face by blinded assessors)

^*^List of specific time points in this row. Carer-QoL = Carer-related Quality of Life questionnaire; CES-D = Centre for Epidemiological Studies – Depression Scale; GSCL = Giessen Subjective Complaints List / Subscale Pain in Limbs; LTS = Leisure Time Satisfaction Measure; RMBPC = Revised Memory and Behaviour Problems Checklist/ subscale frequency; SCQ = Sense of Competence Questionnaire – subscale 2: Satisfaction with one’s own performance as a caregiver; SPSI-R:S = Social Problem-Solving Inventory – revised / subscale: Negative problem orientation; Time burden questionnaire = Including three dimensions of care (1. body care, nutrition, mobility 2. household help IADLs (e.g. housekeeping) 3. additional supervision

It is expected that the multifactorial intervention will have a beneficial impact on participants’ physical activity and functional performance between T1 (pre-intervention) and T2 (post-intervention). Consequently, the primary outcomes include measures of these two domains. It is also expected that participants will report increases in fall related self-efficacy, quality of life, activities of daily living addressed with the assessment within intervention *module 1* and decreases in fear of falling and depressive symptoms. Compared to the control condition, no increases in fall rates are wanted in the intervention group.

The assessments are performed by trained physiotherapists and sport scientists in the participant’s home. All of them are experienced in assessing older, cognitively impaired patients, trained and supervised by the coordinating investigators of the two recruitment sites (KP, KH) and blind to the treatment condition.

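### Blinding of the rater-scored outcomes is at risk: the assessment team makes the weekly falls calls, and the falls diary shares a calendar whose entries differ by arm

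*Protocol article*

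**What the plan says.** The article claims blinding three times without qualification. Methods and design calls the study a "randomised controlled trial with blinded assessors". The legend of Table 3 gives the mode of the participant measures as "participant, face-to-face by blinded assessors". The Outcome measures text after Table 4 describes the assessors as "blind to the treatment condition".

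Other sections fix how falls are captured:

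- **Falls:** "Falls are recorded by implementing falls calendars and weekly telephone calls by the assessment team". Patients and caregivers are asked to complete the diary daily.
- **Applied materials, For participants:** everyone receives a calendar for the "scheduled home visits of the exercise instructor, lay instructor and assessor as well as for keeping a falls and exercise diary". Every calendar also has a page picturing and naming the study team.
- **Control group:** controls receive the calendar for their assessment dates, plus a memory-aid sheet "showing the pictures, names and telephone numbers of the assessors".

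T1, T2 and T3 all take place in the participant's home (Outcome measures).

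**The concern.** Staff declared blind are in weekly contact with patients about the past week. Intervention patients have an MMSE of 17 to 26 and are visited twice a week at home, so an unprompted mention of the visitor or the exercises is easy to imagine. A truthful account of a fall can also reveal the arm, because some falls will happen during intervention visits; the Adverse events section provides for recording these. Separately, the document in which falls are noted also carries the intervention schedule, and it is in the home when the assessor arrives.

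What is at stake is detection bias, probably in favour of the programme:

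- **MADRS and Barthel Index:** the MADRS is scored in a structured interview and the Barthel Index is rated item by item. Both leave room for a rater's expectations.
- **SPPB:** this primary outcome is a performance test run to a set protocol. It is less exposed, but the assessor still conducts and scores it.
- **Walking time:** the other primary outcome comes from a thigh-worn sensor and is largely out of the rater's reach.

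**Working it through.** The article gives no figure for disclosure or for the success of blinding, so there is no stated number to reproduce. The sample size is not affected. The check sets the sections side by side and then asks how exposure accumulates.

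**Route 1, the calendar.**

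1. Table 2 specifies 35 supervised sessions, 32 with the lay instructor alone and 3 joint visits (32 + 3 = 35). The calendar is where scheduled visits are entered, so an intervention calendar can hold up to 35 visits that a control calendar cannot.
2. Exercise entries go in the same diary (For participants; Adherence to intervention protocol).
3. Both arms share the assessment dates. For controls, these are the only calendar use that the Control group section names.
4. The calendar is used at home, and the assessor is in that home at T2 and T3. An assessor who sees it open can infer the arm. This route does not depend on who made the calls.

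**Route 2, the calls.**

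Inputs: weekly calls (Falls); 4 months from T1 to T2 and a further 3 months to T3 (Outcome measures). Assumption: calls run throughout from T1.

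- Calls by T2: 4 × 52/12 = 17.3, taken as 17.
- Calls by T3: 7 × 52/12 = 30.3, taken as 30.

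Let p be the chance that an intervention patient discloses the arm in one call. The documents give no value. Treating calls as independent, P(at least one disclosure) = 1 − (1 − p)^n.

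| p (assumed) | by T2, n = 17 | by T3, n = 30 |
|---|---|---|
| 0.5% | 1 − 0.995^17 = 8% | 14% |
| 1% | 1 − 0.99^17 = 16% | 26% |
| 2% | 1 − 0.98^17 = 29% | 45% |
| 5% | 1 − 0.95^17 = 58% | 79% |

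This is the chance that someone in the team learns the arm. It is not the chance that the T2 rater does. If the T2 rater had made only 4 of the 17 calls (also assumed), the range for p = 0.5% to 5% would be 1 − 0.995^4 = 2% to 1 − 0.95^4 = 19%. If the rater had made none, this route would close apart from talk within the team. The table shows that small risks add up under weekly contact, and that the allocation of calls to staff matters. It does not estimate what happened.

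**The case against.** A reader might infer that the trial's blinding was not delivered. The documents do not support that, for four reasons:

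- No section reports any unblinding.
- The Falls section does not say who collects or reads the calendar, so it is not established that assessors handle it.
- The assessment team comprises several trained staff across two centres, and nothing says that the person who phones a patient also rates that patient.
- A condensed article commonly leaves rotas, call scripts and unblinding logs to the full protocol, so their absence is not a fault.

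All four points stand, and they limit the finding to a risk.

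The calendar contrast also needs care. All participants receive a calendar, and controls must have somewhere to record falls, so two differently printed calendars are not established. What remains is that the handwritten entries will differ, because only one arm has instructor visits to schedule.

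The percentages could fairly be called products of their assumptions. They are, so they serve only as illustration.

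The objection does not remove the core of the point. The article itself assigns the calls to the team it declares blind, and it places the falls record among the intervention entries. Procedures followed as written expose raters to the allocation. That goes beyond a detail left out.

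**Conclusion.** The point holds as a risk. The unqualified blinding statements conflict with two procedures that the article fixes, and the rater-scored outcomes are not well protected: MADRS and Barthel Index most, SPPB less. Walking time is largely protected.

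The size of any bias cannot be derived from the documents. The illustrative 8% to 58% by T2 rests on an assumed per-call disclosure of 0.5% to 5%, independence between calls, and calls running throughout. It refers to the team as a whole. The calendar route comes on top and is not quantified. A possible failure of blinding should not be reported as a proven one, and the trial is not invalidated.

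**What to change.** For the procedures:

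1. Record falls on a separate sheet, identical in both arms, with no visit, exercise or instructor entries. Ask patients to put the calendar and the exercise folder away before T2 and T3.
2. Arrange the calls within the existing team so that nobody rates at T2 or T3 a patient they have phoned.
3. Have the assessor record at T2 and T3 any disclosure and a guess of the allocation, and report both by arm.

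The cost is one extra sheet, one form item and some scheduling effort.

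Recruitment ended in February 2018. With T1 two to six weeks after discharge and T3 seven months after T1, follow-up was probably complete before publication in April 2019. In that case:

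- Report how often caller and rater were the same person, where records allow.
- Repeat the SPPB, MADRS and Barthel comparisons without assessments done by that patient's caller. This criterion applies equally to both arms.
- Do not restrict the analysis to assessments that were not unblinded. Disclosure happens after randomisation and almost only in the intervention arm, so that restriction would select patients differently by arm.
- Qualify the blinding statement for the rater-scored outcomes.

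These steps cost one sensitivity analysis and a sentence in the report. If the call records do not identify the caller, the report should say so.

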##### Quality of life

The Quality Of Life In Alzheimer’s Disease questionnaire (QOL-AD) is a 13-item scale with questions on physical health, mental health, social and financial domains and an overall QOL rating [58]. The QOL-AD was found to be a reliable and valid self-report measure [59, 60]. In addition to the QOL-AD, the validated German version of the EQ-5D™ is used for health economic evaluation [61, 62].

##### Depression

Depressive symptoms are measured with the validated German version of the Montgomery-Åsberg Depression Rating Scale (MADRS) [63, 64]. The scale consists of 10 items, which can be scored from 0 to 6 during a structured interview and is recommended for assessing depressive symptoms in patients with cognitive impairment [65].

##### Activities of daily living

The Barthel Index (BI) consists of 10 items that measure a person’s daily functioning, particularly the activities of daily living and mobility. The items are rated according the Hamburg Classification Manual [66]. In addition, a self-developed questionnaire with 18 items is used to measure the instrumental activities of daily living (IADL) that are displayed on the cards which are used for patient-centred goal-setting (*Module 1*).

#### Other measures

##### Daily activity profiles

For further analysis additional dimensions (e.g. average daily number of steps, number of walking bouts, daily upright duration, daily number of sit-to-stand transfers) are extracted from the activPAL3™ monitoring data.

##### Functional performance

As supplementary measurements for functional performance, kinematic movement parameters are collected by an accelerometer (DynaPort Hybrid, McRoberts, The Hague, The Netherlands) worn at the lower back during the SPPB test. Sway parameters (sway area, sway path) are measured during the static balance subtest, sit-to-stand analysis is added by assessing angular velocity and duration of the fastest sit-to-stand sequence during the five-chair rising subtest [67]. If the patient is unable to rise from a chair (score for chair-rising test = 0), a standardized adaptation of seat height (which allows all patients to stand up without using hands) is allowed for the additional sensor-based sit-to-stand subtest. The selected adaptation is used for all further assessments to allow a comparison of the measures.

##### Pain

Pain intensity is evaluated with the German version of the Western Ontario and McMaster Universities Osteoarthritis –Scale, subscale “pain” (WOMAC) [68, 69].

##### Cognitive performance

Span of memory and working memory resources are assessed with the subscale “repeating numbers” (both forward and backward) of the Nuremberg Age Inventory (NAI: ZN-G) [70].

##### Social support

People providing support in different domains (practical support, emotional support, leisure time activities, confidential issues) are assessed with a modified version of the German Social Support Questionnaire (F-SozU Part B) [71]. It is expected that social support is correlated with physical activity and quality of life [72].

##### Health and intervention costs

Economic evaluation is conducted by recording total formal and informal care costs, acute and sub-acute hospital days, rehabilitation services and total costs of the intervention. If a patient cannot provide adequate information, his caregiver is asked with the permission of the patient to respond in this domain.

##### Adherence to intervention protocol

For *Module 1* the delivery of the card sorting task and goal setting is documented. The total number and frequency of supervised home visits, telephone calls, performed exercises (balance, strength, walking, individual exercises based on goal setting) are recorded by the interventionists and lay instructors. The participants are asked to document any additional exercises in their diaries. Non-adherence is defined if at least one of the following criteria is met: (a) less than two joint home visits of the interventionist and lay instructor, or (b) less than 19 of the targeted 32 home visits by the lay instructor without interventionist. For *Module 2* the frequency and time of face-to-face and telephone contacts with the patients (and their caregivers) are documented. In counselling scenarios without caregivers non-adherence is defined only by the missing home visit.

#### Secondary outcome measures and other measures (participating caregiver)

It is assumed that less than 50% of the patients have family caregivers who meet the inclusion criteria and consent to participate in the study. In contrast to own previous caregiver intervention studies [30, 46], caregivers are included in this study also without showing significant burden, caregiving stress behaviours or depressive symptoms. Therefore, it is expected that the statistical power is not sufficient to detect statistically significant differences in caregiver outcomes between the groups. But with measuring depressive symptoms (CES-D) [73, 74], perceived caregiver competence (SCQ; subscale two: Satisfaction with one’s own performance as a caregiver) [75, 76], quality of life (CarerQoL) [77], physical complaints (GSCL-24; subscale pain in limbs) [78], social problem-solving abilities (SPSI-R:S; subscale: negative problem orientation [79] [80]), leisure time satisfaction (LTS) [81], and frequency of the patients´ behavioural symptoms (RMBPC; subscale frequency) [82], intervention effects can be compared with previous caregiver interventions. Further information on the caregiver outcome measures are published elsewhere [46].

##### Adherence to intervention protocol

The frequency and time of face-to-face and telephone contacts with the participating caregiver are documented. Non-adherence is defined if at least one of the following criteria is met: (a) no home visit/face-to-face contact or (b) total time of follow-up telephone calls less than 45 min.

### Adverse events

In this trial a serious adverse event (SAE) is defined as any harmful disease or injury, fall-related or not, that leads to hospital admission or death [83]. Furthermore, all falls which happen during assessment or intervention independent of severity are recorded as SAE as well. Any minor or temporary clinical symptoms are only recorded as adverse events if they result in considerable restricted daily activities (e.g. staying in bed) for more than one week. All SAEs are documented according to the trial protocol. SAEs within the intervention and SAEs that requires further action beyond the study protocol (e.g. involving local services because the patient is not able to organize additional support) are directly discussed with the investigators (KP, KH, MS). In addition, the SAE documentation is discussed annually with at least one member of the independent data and safety monitoring committee (DSMC).

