**Fig. 2 Fig2:**
[figure not shown]
Flow of intervention

The intervention group and the control group both have regular access to standard care during the whole study. Hence, the intervention is an add-on to usual care. To establish a minimum standardization of recommendations given before discharge at both recruitment sites, all participants receive the same face-to-face advice session (max. 60 min) on recommended regular physical exercises and tips for fall prevention. The addressed issues are based on an illustrated advice booklet [27] given to all participants. For those with difficulties in understanding the recommendations, this session can be repeated or, if existing, caregivers are asked to attend.

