Training progression	(a) ‘Standing‘(initial position: upright bipedal stance) • With reduction of base of support: Feet shoulder-width apart ➔ side-by-side ➔ semi-tandem ➔ tandem ➔ one-legged stance • With/ without holding at table • With head movement • With eyes closed (b) ‘Weight shifting‘(initial position: upright bipedal stance) • Weight shifting sideways: With feet on the floor ➔ with raising heel of unloaded leg ➔ with lifting foot (and holding position) • Weight shifting forwards/backwards: Stride stance ➔ with raising posterior heel when shifting forwards • With/ without holding at table (c) ‘Walking’ • Small steps/ big steps/ small track width • Sideways/ backwards • From slow to fast movement velocity • With/ without double or one hand contact, with/ without walking aid (d) ‘Chair-rising’ • With booster seat if necessary (15 cm ➔ 10 cm ➔ 5 cm ➔ without booster seat) • With/ without double hand contact, with/without using armrest • From slow to fast movement velocity	
Intensity	(a) ‘Standing‘and (b) ‘Weight shifting‘ • 10–12 repetitions of10 s, including 4–6 repetitions of moderate level of difficulty and 6 repetitions of maximum level of difficulty (c) ‘Walking‘(distance 2–4 m) • 10–12 repetitions, including 7–9 repetitions of moderate level of difficulty and 3 repetitions of maximum level of difficulty (d) ‘Chair-rising’ • 5 series of 5 repetitions, including 2 series of moderate level of intensity and 3 series of higher level of intensity	
Volume	• Overall: 4-month training program • Each session (supervised): 30 min (as component of one home visit of maximally 2 h duration which further includes practicing of at least one meaningful activity and possible additional time for unstandardized interaction, e.g. conversation) • Additional self-exercise session (unsupervised or with caregiver): 10–20 min	
Frequency	• 2 supervised exercise sessions per week with a total of 35 sessions (including 32 visits with lay instructor alone, and 3 visits with lay instructor + interventionist)	• 3–4 recommended self-exercises on days without supervised exercise sessions • Frequency and time depending on patient’s capacity and caregiver’s support

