##### Visits of the lay instructors

After the initial home visit, regular home visits with exercise supervision by the lay instructor are conducted over four months with a frequency of two times per week. Each home visit takes maximally two hours including (a) 30 min for exercises, (b) practicing of at least one further physical activity according to the participant’s personal goals and (c) additional time for unstandardized interaction (e.g. conversation) comparable to usual visits provided by visitor services. All home visits and supervised exercises are recorded by the lay instructor. In accordance to previous work on peer-delivered physical activity and exercise interventions [41, 42], the authors could show in the pilot study with 17 cognitively impaired hip and pelvic fracture patients that the designed intervention approach with lay instructors is feasible and effective ([name], [name]: Hip fracture and cognitive impairment: Pilot study of a post-rehabilitation exercise program, unpublished).

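### Every fall during an intervention visit is an SAE whatever its severity, and only one arm has those visits, so any SAE total by arm is tilted against the intervention

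*Protocol article*

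**What the plan says.** The Adverse events section sets three thresholds.

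- An SAE "is defined as any harmful disease or injury, fall-related or not, that leads to hospital admission or death".
- The section then adds: "Furthermore, all falls which happen during assessment or intervention independent of severity are recorded as SAE as well".
- Minor or temporary symptoms are "only recorded as adverse events if they result in considerable restricted daily activities (e.g. staying in bed) for more than one week".

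The same section says that SAEs within the intervention are discussed directly with the investigators, and that SAE documentation is discussed once a year with at least one DSMC member. Under Ethics and dissemination, the DSMC may recommend that the trial continue, be modified or stop.

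Exposure to the second threshold differs by arm. For the intervention arm, Table 2 gives "2 supervised exercise sessions per week with a total of 35 sessions", and the section on lay instructors' visits says "Each home visit takes maximally two hours including (a) 30 min for exercises". For the other arm, "Participants allocated to the control group have usual access to standard care", plus a calendar and a contact sheet. Two settings are shared: the four assessment time points (Outcome measures), and the session before discharge described in the intervention overview, where "all participants receive the same face-to-face advice session (max. 60 min)".

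**The concern.** Two severity thresholds share one label, and where a fall happens decides which applies. A patient who goes to the floor unhurt during a home visit has an SAE. A patient in either arm who does the same at home outside a visit does not, and may not reach the adverse event threshold either. Only one arm spends time in intervention visits, and the supervised tasks are deliberately set near the limit of what the patient can do safely. The excess from this source can run in one direction only.

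What is at stake is how an SAE total split by arm would be read. If non-serious falls in visits are pooled with admissions and deaths, the intervention arm can show more serious events with no more serious harm. A DSMC member or a later reader who sees only the pooled total could not tell the two apart.

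**Working it through.** The article gives no SAE rate or SAE comparison to reproduce. The check sets the definitions side by side, counts exposure from the article's figures, and then shows a range under declared assumptions.

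**1. Which falls count as an SAE if they do not lead to admission or death**

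| Setting | Intervention arm | Control arm |
|---|---|---|
| Assessment | SAE | SAE |
| Advice session before discharge, if it counts as intervention | SAE | SAE |
| Supervised home visit | SAE | no such visits |
| At home, outside any visit | not an SAE | not an SAE |

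Only the third row differs between arms.

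**2. Exposure in that row**

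- Exercise time only: 35 × 0.5 h = 17.5 h per intervention patient.
- Full visit at its maximum length: 35 × 2 h = 70 h.
- Control: 0 h.
- Four months at an assumed 16 waking hours a day is 4 × 365.25/12 × 16 = 1,948 h, so the exposure is 17.5/1,948 = 0.9% to 70/1,948 = 3.6% of waking time.

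**3. Illustrative number of falls in visits**

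The article gives no fall rate. Assume 0.5 to 3 falls per person-year, spread over 365.25 × 16 = 5,844 waking hours, and a relative risk (RR) during visits of 1 to 3. With 120 patients per arm (Sample size) and every visit delivered:

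expected falls = 120 × 35 × hours per visit × (annual rate / 5,844) × RR

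| Falls per person-year | 0.5 h, RR 1 | 0.5 h, RR 3 | 2 h, RR 1 | 2 h, RR 3 |
|---|---|---|---|---|
| 0.5 | 0.18 | 0.54 | 0.72 | 2.16 |
| 1 | 0.36 | 1.08 | 1.44 | 4.31 |
| 2 | 0.72 | 2.16 | 2.87 | 8.62 |
| 3 | 1.08 | 3.23 | 4.31 | 12.94 |

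The range is about 0.2 to 13. Two features make it generous. First, it assumes full attendance. If only 85 of 120 patients were followed through and the rest had no visits, it becomes 0.18 × 85/120 = 0.13 to 12.94 × 85/120 = 9.2. Second, any of these falls that led to admission would be an SAE under the general criterion anyway.

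**4. What this does to a proportion**

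Assume a true SAE risk of 30% in both arms and, independently, a non-serious fall in a visit in a fraction q of intervention patients. The recorded intervention risk is 1 − (1 − 0.30)(1 − q):

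- q = 2%: 31.4%, risk ratio 1.05
- q = 5%: 33.5%, risk ratio 1.12
- q = 10%: 37.0%, risk ratio 1.23

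The true risk ratio is 1 in each case. If SAEs in both arms are counted on the admission-or-death rule alone, the structural excess is 0.

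**The case against.** The strongest reply is that the article fixes a recording rule and not an analysis. Under Data analyses, ANCOVA is planned for the primary and secondary endpoints. SAEs are not among them, and no SAE test, table by arm or stopping boundary is stated. How SAEs are tabulated may sit in an analysis plan or a DSMC charter that is not shown. This stands. A reader might infer that the trial has a planned safety comparison that is biased, or that the DSMC is shown SAE counts by arm. The article says neither. The point holds for any count by arm that is made, and rests on the stated definition.

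It is also fair to say that the between-arm question on falls has its own outcome: calendars and weekly telephone calls, with one definition for both arms. Admissions and deaths are likewise defined identically in both arms. Both remarks stand. A reader might go further and infer that the rule corrupts the evidence on admissions and deaths. It does not; it can obscure them only for someone who sees the pooled total alone.

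The size is open to challenge too. Taking 120 × 35 = 4,200 visits and one fall per 1,000 to 200 visits would give about 4 to 21 extra SAEs. With two-hour visits, however, those rates equal 5,844/(2 × 1,000) = 2.9 to 5,844/(2 × 200) = 14.6 falls per person-year, and they presume full attendance. The article supports no such rate.

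Finally, recording every supervised fall is a cautious choice when lay instructors lead the exercises, and any tilt runs against the intervention. That justifies the recording. It does not justify pooling those falls with admissions and deaths when arms are set side by side.

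**Conclusion.** The point holds as one about tabulation. By its stated definition, a total SAE count by arm is tilted against the intervention, because a rule without a severity threshold applies to 17.5 to 70 hours of visits per intervention patient and to none in control. Falls at assessments and in the advice session fall under the same rule in both arms and are not the source of the tilt.

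The direction follows from the text alone. The size does not: 0.2 to 13 extra recorded SAEs per 120 patients depends on the assumed fall rates, the assumed relative risk during visits and full attendance, and its lower end is close to nothing. The article supports no claim that a planned comparison is invalid, or that the falls outcome or the count of admissions and deaths is affected. The change is still worth making, because a DSMC that can recommend stopping, or a reader of published totals, should see counts made on one rule in both arms.

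**What to change.** In any SAE table or DSMC review split by arm, count as SAE only events that lead to hospital admission or death. List falls during intervention visits and falls during assessments as a separate category, shown apart from each other and described per visit or per assessment. Falls during visits should not be compared between arms, since control has no such visits. A fall in either setting that leads to admission or death stays in the SAE count as well.

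Recording of these falls and their immediate discussion with the investigators stay as they are. Recruitment ran to February 2018, so this concerns presentation only. The article already treats SAEs within the intervention as a recognisable group, so the records should allow the split. The cost is one sentence in the plan and a little re-tabulation, with no safety information lost.
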